###### 1st Step in the Pregnancy Episode Algorithm: Assignment of Outcomes

An outcome assessment hierarchy rational was chosen similar to that used in a study by Mikolajcyzk et al. Births unambiguously indicate the outcome took place, however spontaneous abortions and ectopic pregnancies may only indicate suspicion of occurrence of the event so these will be assessed after birth outcomes [[11](#_ENREF_11)]. Valid outcomes will be assessed in this order:

- Live birth (at least one)
- Stillbirth
- Delivery-Live birth or stillbirth
- Trophoblastic Disease
- Ectopic pregnancy
- Induced abortion
- Spontaneous abortion

Before searching for outcomes, remove all patients from consideration who only have gestational diabetes screening (DIAB) records without any other pregnancy categories, as urine and serum glucose tests have low specificity for pregnancy.

Outcomes will be found in the CDM condition_occurrence, procedure_occurrence and observation files. In addition to SNOMED-CT and procedure concepts in the CPRD CDM:

- live births can be indicated by LOINC concepts when the value_as_string field in the observation table=’Live birth’ or ‘Neonatal death’
- stillbirths can be indicated by LOINC concepts when the value_as_string field in the observation table=’Still birth’ or ‘Intra-partum death’
- deliveries can be indicated by LOINC concepts when the value_as_string field in the observation table=’Unknown’

The following steps assign the valid pregnancy outcomes:

1. Valid live birth (LB) outcomes will be assessed first. Starting with the first LB outcome (assumed to be true), the 2^nd^ LB outcome will be assessed to see if it occurs after the necessary time interval (see Table 1). Table 1 contains time windows that are based on the least amount of time a 2^nd^ outcome can happen after the 1^st.^  These can change based upon the specific outcomes under consideration. Minimum time allowed between two LB outcomes is 182 days. These time windows were adapted from the Hornbrook et al.[[1](#_ENREF_1)] algorithm and validated by in-house medical experts. If the 2^nd^ LB outcome happens too soon after the 1^st^, it will be removed from consideration and the 3^rd^ LB outcome will be compared to the 1^st^ LB outcome in the same manner. If the 2^nd^ LB outcome occurs after the time window allowed it will be classified as a valid outcome, and the 3^rd^ LB outcome will be compared to it; this process will be repeated until all LB outcomes for a patient are assessed.

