2. Next, all stillbirth (SB) outcomes will be assessed. The first SB outcome found for a patient will be compared to all LB outcomes determined to be valid for the patient in the prior step. If all LB outcomes prior to the SB outcome occur 168 days prior to the SB outcome and all LB outcomes after the SB outcome occur 182 days after the SB outcome then the first SB outcome will be added to the valid outcome set. Each subsequent SB outcome will be assessed for validity in this manner against all LB and SB outcomes that have been determined to be valid using Table 1 in the prior step. In other words, if all outcomes prior to the subsequent SB outcome are prior to the minimum number of days for that outcome combination in Table 1 and all outcomes after the subsequent SB outcome are after the minimum number of days for that outcome in Table1 then the subsequent SB outcome will be added to the outcome set.
3. Next, all delivery (DELIV) outcomes will be assessed against all valid LB, SB and DELIV outcomes in the same manner as described above for SB and added to the valid outcome set if Table 1 criteria is met.
4. Next, ectopic pregnancy (TRO) outcomes will be assessed against all valid LB, SB, DELIV, and TRO outcomes in the same manner as described above for SB and added to the valid outcome set if Table 1 criteria is met. In order to eliminate TRO rule-out diagnoses, if there is an antenatal GP visit, pregnancy confirmation or pregnancy complication record within 42 days of the TRO record that TRO outcome will not be added to the valid outcome set.
5. Next, ectopic pregnancy (ECT) outcomes will be assessed against all valid LB, SB, DELIV, TRO and ECT outcomes in the same manner as described above for SB and added to the valid outcome set if Table 1 criteria is met. In order to eliminate ECT rule-out diagnoses, if there is an antenatal GP visit, pregnancy confirmation or pregnancy complication record within 42 days of the ECT record that ECT outcome will not be added to the valid outcome set.
6. Next, induced abortion (AB) outcomes will be assessed against all valid LB, SB, DELIV, TRO, ECT and AB outcomes in the same manner as described above for SB and added to the valid outcome set if Table 1 criteria is met.

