7. Next, spontaneous abortion (SA) outcomes will be assessed against all valid LB, SB, DELIV, TRO, ECT, AB, and SA outcomes in the same manner as described above for SB and added to the valid outcome set if Table 1 criteria is met. In order to eliminate SA rule-out diagnoses, if there is an antenatal GP visit, pregnancy confirmation or pregnancy complication record within 42 days of the SA record that ECT outcome will not be added to the valid outcome set.

| Table 1: Minimum Number of Days Required to Identify Separate Pregnancy Outcomes | | |
| --- | --- | --- |
| First Pregnancy Outcome | Second Pregnancy Outcome | Minimum Days Between Outcomes |
| LB | LB | 182 |
| LB | SB | 168 |
| LB | DELIV | 168 |
| LB | TRO | 70 |
| LB | ECT | 70 |
| LB | AB | 70 |
| LB | SA | 70 |
| SB | LB | 182 |
| SB | SB | 168 |
| SB | DELIV | 168 |
| SB | TRO | 70 |
| SB | ECT | 70 |
| SB | AB | 70 |
| SB | SA | 70 |
| DELIV | LB | 182 |
| DELIV | SB | 168 |
| DELIV | DELIV | 168 |
| DELIV | TRO | 70 |
| DELIV | ECT | 70 |
| DELIV | AB | 70 |
| DELIV | SA | 70 |
| TRO | LB | 168 |
| TRO | SB | 154 |
| TRO | DELIV | 154 |
| TRO | TRO | 56 |
| TRO | ECT | 56 |
| TRO | AB | 56 |
| TRO | SA | 56 |
| ECT | LB | 168 |
| ECT | SB | 154 |
| ECT | DELIV | 154 |
| ECT | TRO | 56 |
| ECT | ECT | 56 |
| ECT | AB | 56 |
| ECT | SA | 56 |
| AB | LB | 168 |
| AB | SB | 154 |
| AB | DELIV | 154 |
| AB | TRO | 56 |
| AB | ECT | 56 |
| AB | AB | 56 |
| AB | SA | 56 |
| SA | LB | 168 |
| SA | SB | 154 |
| SA | DELIV | 154 |
| SA | TRO | 56 |
| SA | ECT | 56 |
| SA | AB | 56 |
| SA | SA | 56 |

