### Data Quality Assurance

#### Validation Procedures

The primary data quality assurance activities are performed through the development of OMOP CDM, which is documented elsewhere (<http://omop.org/CDM> ).

The analysis will be programmed by a member of the Janssen Global Epidemiology Analytics team. A second programmer will perform an independent quality assurance review of all source code and analysis results to confirm the work performed is consistent with what is described in this protocol before the results are shared with the investigator team.

Validation efforts will include a review of 50 CPRD and 50 Optum randomly drawn pregnancy episodes from each outcome (6 outcomes X 50 X 2) for a total of 600 profiles by clinical personnel. An extra 50 profiles for LB outcomes for each database will also be reviewed because the majority of pregnancy episodes result in a live birth. Proportion of episodes which refer to an actual pregnancy, proportion of episodes with correct outcome and proportion of episodes with correct start date (or plausible start date if inferred) for each database will be determined.

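### Item 7 of outcome assignment acts on ECT where its purpose and trigger say SA, so as written the 42-day rule-out filter rejects no spontaneous abortion record

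*Protocol*

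**What the plan says.** The Protocol section *1st Step in the Pregnancy Episode Algorithm: Assignment of Outcomes* explains that "spontaneous abortions and ectopic pregnancies may only indicate suspicion of occurrence of the event", and places these outcomes after births in the assessment order. Three outcomes then receive a rule-out filter based on a nearby antenatal, confirmation or complication record:

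- Item 4, trophoblastic disease (TRO): "within 42 days of the TRO record that TRO outcome will not be added to the valid outcome set".
- Item 5, ECT: "within 42 days of the ECT record that ECT outcome will not be added to the valid outcome set".
- Item 7, SA. The purpose and condition are "In order to eliminate SA rule-out diagnoses, if there is an antenatal GP visit, pregnancy confirmation or pregnancy complication record", and the sentence ends with the action: "pregnancy complication record within 42 days of the SA record that ECT outcome will not be added to the valid outcome set".

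Item 4 opens with "Next, ectopic pregnancy (TRO) outcomes will be assessed against all valid LB, SB, DELIV, and TRO outcomes", although the category table under *Concept Code List* defines TRO as trophoblastic disease.

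Under *Validation Procedures*, a second programmer reviews the source code and results to "confirm the work performed is consistent with what is described in this protocol".

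**The concern.** In items 4 and 5 the outcome that triggers the filter is the outcome withheld. In item 7 the trigger is an SA record and the outcome withheld is an ECT. The item mentions no ECT to which the phrase could refer, and no other section gives SA a rule-out filter. The stated purpose is therefore not achieved by the stated rule.

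This sentence is an operative instruction. One standard program is to be run on all four databases, and quality control compares that program with this text. A literal program would agree with the action as worded, while a program that filters SA would depart from it.

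Two results are at stake, and both belong to the primary objective of determining episodes and their outcomes. Suspected miscarriages in pregnancies that continued could enter the SA cohort. A false SA also becomes a prior outcome for the birth that follows, and the start-date rules use the prior outcome to limit how far back they search.

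**Working it through.** **1. The three filters side by side**

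| Item | Stated purpose | Trigger record | Outcome withheld |
| --- | --- | --- | --- |
| 4 | remove TRO rule-outs | TRO | TRO |
| 5 | remove ECT rule-outs | ECT | ECT |
| 7 | remove SA rule-outs | SA | ECT |

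Only item 7 is mismatched. Taken literally, the one remaining test on an SA record is the Table 1 spacing.

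**2. How much the spacing catches**

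Inputs: Table 1 minimum from SA to live birth (LB), 168 days; Table 2 SA term range, 28 to 133 days; Table 4 LB gestational estimates, 245, 280 and 285 days. The SA range contains 133 − 28 + 1 = 106 days.

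An SA record on gestational day g, in a pregnancy that ends in a live birth on day L, passes if L − g ≥ 168, that is, if g ≤ L − 168. The minimum is taken as inclusive.

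| L | Latest passing day | Passing days | Count |
| --- | --- | --- | --- |
| 245 | 245 − 168 = 77 | 28–77 | 50 of 106 |
| 280 | 280 − 168 = 112 | 28–112 | 85 of 106 |
| 285 | 285 − 168 = 117 | 28–117 | 90 of 106 |

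These are counts of calendar days, not shares of records.

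**3. One pregnancy followed through (assumed dates)**

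Last menstrual period (LMP) on day 0, suspected SA on day 60, antenatal visit on day 74, live birth on day 280, no earlier outcome.

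- Spacing: 280 − 60 = 220 ≥ 168, so the SA passes.
- Item 7 as written: the SA is kept.
- Item 7 with SA in the action: 74 − 60 = 14 ≤ 42, so the SA is rejected.

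**4. Effect on the live-birth start date if the SA is kept**

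The start-date section does not define the retry count. I take it to be the last column of Table 2, which is 14 days after an SA. LB maximum and minimum terms are 301 and 161 days.

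- The search window opens at the larger of 280 − 301 = −21 and 60 + 14 = 74, so on day 74.
- It closes at 280 − 161 = day 119.
- The true LMP on day 0 lies outside the window, as does any gestational-age, nuchal ultrasound or AFP estimate close to day 0.
- Step 5, full term or no term data: 280 − 280 = 0, which is earlier than 74, so the start is set to day 74.
- Step 6 accepts only markers inside the same window, so it cannot move the start earlier.
- Episode length: 280 − 74 = 206 days instead of 280.

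The LMP goes to the false SA instead, because the SA window runs from 60 − 133 = −73 to 60 − 28 = 32 and contains day 0.

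With the same inputs and no dating record inside the shortened window, the live birth starts g + 14 days late. Over the passing days 28 to 112, that is 42 to 126 days.

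**The case against.** The strongest reply is that the slip corrects itself. The sentence opens by naming SA, its trigger is an SA record, and items 4 and 5 show the pattern. The ECT in the action has no referent, so a careful programmer would code SA or raise a query. A second programmer who reads the purpose clause might expose the mismatch. This argument stands as to intent and makes a literal implementation less likely. It does not make the written rule correct, and the quality check is defined by that written rule.

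Four stronger readings are tempting, and the documents do not support them:

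- **SA records go wholly unfiltered.** They do not. Table 1 still rejects 106 − 85 = 21 of 106 days before a 280-day birth and 106 − 50 = 56 of 106 before a 245-day birth. Threatened abortion also has its own category, separate from SA.
- **Valid ectopics are deleted.** Item 7 withholds an outcome from being added. ECT outcomes were added in item 5, and no step removes an outcome already in the set.
- **A given percentage of the SA cohort is false.** The documents give no share of SA codes that are rule-outs. The 13% SA share in *Background* is a final episode share from another algorithm in another health system and cannot be scaled into one.
- **Item 4 assesses the wrong condition.** The code TRO is used throughout that item and is defined elsewhere as trophoblastic disease. Only the descriptive label is wrong.

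It is also fair to say that the 42-day window has no stated direction. Once SA is named, a genuine miscarriage with a pregnancy confirmation shortly before it would be rejected too. The net effect of the intended filter on the SA cohort is therefore not established. Items 4 and 5 share that feature, and it is separate from the question of which outcome item 7 acts on.

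Clinical profile review of 50 episodes per outcome might reveal false SA episodes, but only after the episodes are built and only in CPRD and Optum. It is described as covering six outcomes when there are seven cohorts, without saying which is left out.

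**Conclusion.** Item 7 is wrong as written: its action contradicts its own purpose and trigger. If it is followed literally, no SA record is rejected by the rule-out filter, and Table 1 spacing is the only remaining test. That spacing leaves 85 of 106 possible SA days open before a 280-day live birth (50 for 245 days, 90 for 285). A false SA kept in this way can also shorten the following live-birth episode, in the worked case from 280 to 206 days.

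The day counts rest only on Tables 1, 2 and 4. The shortened episode also rests on assumed dates and on reading the retry count as the last column of Table 2. How many episodes would be affected cannot be derived from the documents, and whether the program follows the literal text is unknown. The finding is a definite error in an operative rule with a plausible route to harm, not a demonstrated bias of known size.

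**What to change.** In item 7, change the outcome named in the action from ECT to SA, so that it agrees with the item's purpose and trigger. Confirm that the program withholds the SA outcome, and do this before the second programmer compares code with protocol. If episodes have already been built from code that follows the literal text, rerun outcome assignment and then start-date assignment, since the second depends on the first.

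As an editorial correction in the same revision, relabel TRO in item 4 as trophoblastic disease.

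The cost is one word in an operative rule, one label and a short code check. No new data or design change is needed.

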###### 2nd Step in the Pregnancy Episode Algorithm: Assignment of Start Dates

In the pregnancy episode algorithm time periods need to be defined for various elements in order to calculate pregnancy start date. In Table 2 below the following time periods for each outcome are defined:

- Maximum pregnancy term - amount of time to search back from the outcome for all pregnancy markers. This time period should be the longest possible gestation period for an outcome so as to capture early markers.
- Minimum pregnancy term - Shortest possible gestational period for each outcome.
- Number of days a 2^nd^ pregnancy is possible after the outcome – This time window indicates how many days after the outcome specified another pregnancy may be initiated.

All time windows were estimated from research specific to each outcome and validated by in-house clinical experts.

| **Table 2: Time windows in days necessary to calculate pregnancy episode start date** | | | |
| --- | --- | --- | --- |
| **Outcome** | **Maximum Pregnancy Term** | **Minimum Pregnancy Term** | **Days 2nd pregnancy possible after outcome** |
| **LB** | 301 | 161 | 28 |
| **SB** | 301 | 140 | 28 |
| **DELIV** | 301 | 140 | 28 |
| **TRO** | 112 | 42 | 14 |
| **ECT** | 84 | 42 | 14 |
| **AB** | 168 | 42 | 14 |
| **SA** | 133 | 28 | 14 |

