**Pregnancy Episode Start Date Calculation**

To calculate pregnancy episode start date possible start dates will be assigned in the following hierarchy (final start date chosen will be first one assigned in hierarchy):

**Step 1:** LMP (last menstrual period) date as start of pregnancy episode:

1. If LMP records exists between (larger of maximum term allowed subtracted from outcome date or prior outcome date plus retry count) and minimum term allowed subtracted from outcome date then LMP becomes the pregnancy start date
2. If there are more than one LMP records in the live birth window, use the latest so as not to grab a LMP record from an earlier pregnancy episode
3. ~50% of CPRD live births will have an LMP value (median pregnancy length 280 days using LMP date as start of episode); no US claims live births will

**Step 2:** GEST (gestational age in weeks) date as start of pregnancy episode:

1. In CPRD, for GEST record use string_as_value from observation table or in CPRD or US CLAIMS use gest_value from pregnancy concept file, whichever is present. Only use GEST values between 0 and 42 weeks.
2. If GEST record date-(GEST value*7) +1 exists between (larger of maximum term allowed subtracted from outcome date or prior outcome date plus retry count) and minimum term allowed subtracted from outcome date then GEST record date-(GEST value*7) +1 becomes the pregnancy start date.
3. If there are more than one GEST records in the allowed time window, use the latest so as not to grab a GEST record from an earlier episode
4. ~28% of CPRD live births will have a GEST value and not a LMP value with a median pregnancy length 279 days (in CPRD GEST codes are used for any outcome in the additional file); 1.4% of Optum live births will have a GEST value with a median pregnancy length 230 days (in OPTUM GEST codes are used primarily to record a premature birth)

**Step 3:** NULS (nuchal ultrasound) date as start of pregnancy episode:

1. If NULS date-89 exists between (larger of maximum term allowed subtracted from outcome date or prior outcome date plus retry count) and minimum term allowed subtracted from outcome date then NULS date-89 becomes the pregnancy start date.
2. If there are more than one NULS records in the allowed time window, use the first so as to use the NULS date that is most likely the recommended date in clinical guidelines rather than a repeat test.

**Step 4:** AFP (alpha fetoprotein test) date as start of pregnancy episode:

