1. If AFP date-123 exists between (larger of maximum term allowed subtracted from outcome date or prior outcome date plus retry count) and minimum term allowed subtracted from outcome date then AFP date-123 becomes the pregnancy start date.
2. If there are more than one AFP records in the allowed time window, use the first so as to use the AFP date that is most likely the recommended date in clinical guidelines rather than a repeat test.

**Step 5:** Outcome specific estimates:

1. If at least one PREM (premature term pregnancy), POSTT (post term pregnancy) or FT (full term pregnancy) record exists between (larger of maximum term allowed subtracted from outcome date or prior outcome date plus retry count) and 30 days after outcome date then categorize pregnancy as PREM, POSTT or FT.
2. If combinations of PREM, POSTT, FT records exist in this time window, categorize pregnancy in this order: 1) PREM if present, 2) POSTT if present, 3) FT if present.
3. Based on Table 4, choose an outcome specific gestational age estimate based on outcome and term and subtract from outcome date to obtain a pregnancy start date. If prior outcome date plus retry count is greater than outcome date minus outcome specific gestational age estimate then pregnancy start date becomes prior outcome date plus retry count.

**Step 6**: Choose final pregnancy start date:

1. Choose the best pregnancy start date (first one assigned in steps 1-5).
2. If a PCONF (pregnancy confirmation), AGP (antenatal GP visit) or OTEST (other pregnancy test) category records exist between (larger of maximum term allowed subtracted from outcome date or prior outcome date plus retry count) and minimum term allowed subtracted from outcome date and is prior to the best start date as calculated in the prior 5 steps then the first found PCONF, AGP or OTEST becomes pregnancy start date.

Table 4 provides outcome specific gestational age estimates for all outcomes for premature, post and full term pregnancies. These outcome specific gestational age estimates were obtained from Hornbrook et al.[[1](#_ENREF_1)] and Margulis et al. and were validated by in-house clinical experts and should represent average gestational times for the outcomes and terms.

| **Table 4: Outcome Specific Gestational Age Estimates in Days** | | | | |
| --- | --- | --- | --- | --- |
| **Outcome** | **PreTerm** | **PostTerm** | **FullTerm** | **NoData** |
| **LB** | 245 | 285 | 280 | 280 |
| **SB** | 196 | 285 | 280 | 196 |

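### Table 2 leaves gestations of 134 to 139 days outside the spontaneous abortion, stillbirth and delivery windows, so a correct recorded start in that band is rejected and may be replaced by a default about two months off

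*Protocol*

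**What the plan says.** The section on assignment of start dates (2nd Step) defines the two limits in Table 2. The maximum term is the search-back period: "This time period should be the longest possible gestation period for an outcome so as to capture early markers". The minimum term is the "Shortest possible gestational period for each outcome". The SA row has a maximum of 133 and a minimum of 28 days. The SB row has 301 and 140, and the delivery row is the same: "DELIV | 301 | 140 | 28".

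The section Pregnancy Episode Start Date Calculation uses these limits as filters:

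- **Step 1** takes an LMP only if it lies between the outcome date minus the maximum term (or the prior outcome plus retry count, if later) "and minimum term allowed subtracted from outcome date then LMP becomes the pregnancy start date".
- **Step 2** applies the same window to gestational-age (GEST) records, where "GEST record date-(GEST value*7) +1 becomes the pregnancy start date".
- **Steps 3 and 4** do the same for the nuchal scan date minus 89 days and the AFP date minus 123 days.
- **Step 5** is the fallback: "choose an outcome specific gestational age estimate based on outcome and term and subtract from outcome date to obtain a pregnancy start date". Table 4 gives SA 70 days in every column. For stillbirth the row (preterm, post-term, full-term, no data) reads "SB | 196 | 285 | 280 | 196".
- **Step 6** looks in the same window for a pregnancy confirmation, antenatal visit or other pregnancy test earlier than the chosen start; "then the first found PCONF, AGP or OTEST becomes pregnancy start date".

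**The concern.** By the protocol's own definitions, a spontaneous loss cannot occur after day 133 and a stillbirth cannot occur before day 140. A loss at 19 weeks 1 day to 19 weeks 6 days is then impossible under either code. Nothing in the text says that this is intended.

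Because the windows are hard filters, the gap has a practical effect: a correct recorded date is discarded and an average may take its place. The primary objective is to evaluate episode start, end and outcome, including outcomes other than live birth, and the descriptive analyses will review pregnancy terms by outcome. A loss in this band truly falls in week 20, the second trimester under Study Design (weeks 14 to 26). With the 70-day default it appears at the end of week 10, in the first trimester. With the 196-day default it appears at the end of week 28, in the third.

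**Working it through.** The protocol gives no derivation of the Table 2 limits, so there is no figure to reproduce. The check applies the rules as written, with inclusive limits (an assumption; exclusive limits would widen the gap). A start is accepted if minimum term ≤ outcome date − start date ≤ maximum term.

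**1. The gap.** SA accepts 28 to 133 days (133 = 19 × 7). SB and DELIV accept 140 to 301 days (140 = 20 × 7). The uncovered days are 134, 135, 136, 137, 138 and 139. Among all outcomes only induced abortion (42 to 168) covers them.

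**2. LMP in the band.** For a loss at 134 to 139 days with a correct LMP, Step 1 rejects it as too long if coded SA and too short if coded SB.

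**3. Step 5 default.**

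| Code | Table 4 value | Error at 134 days | Error at 139 days |
|---|---|---|---|
| SA | 70 | 134 − 70 = 64 days too late | 139 − 70 = 69 days too late |
| SB, preterm or no term record | 196 | 196 − 134 = 62 days too early | 196 − 139 = 57 days too early |

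**4. GEST records.** With a record on the outcome date, episode length = 7 × weeks − 1.

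- 19 weeks: 7 × 19 − 1 = 132 days. Accepted for SA, with an error of 134 − 132 = 2 to 139 − 132 = 7 days. Rejected for SB.
- 20 weeks: 7 × 20 − 1 = 139 days. Above 133 and below 140, so rejected under both codes. If weeks are completed weeks (assumption), the true gestation is 140 to 146 days, inside the SB window. Without an LMP, the SB default is then 196 − 146 = 50 to 196 − 140 = 56 days too early.

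**5. Screening tests, loss at g days, test at gestational day s.**

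- Nuchal: length = g − s + 89. For SA this must be at most 133, so s ≥ g − 44, which is day 90 (g = 134) to day 95 (g = 139) or later.
- AFP: length = g − s + 123, so s ≥ g − 10, which is day 124 to day 129 or later.
- For SB, length must be at least 140, so early tests pass: nuchal at s ≤ g − 51 (day 83 to 88), AFP at s ≤ g − 17 (day 117 to 122).

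**6. Step 6.** For SA, an earlier marker in the window becomes the start, so the error equals the gestational age at that marker: 42 to 56 days if it is at 6 to 8 weeks. For SB, Step 6 only moves the start earlier, which adds to an error that is already too early.

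**7. With an SA maximum of 139.** No gestation lies outside both windows. An LMP 134 to 139 days before an SA-coded loss is accepted, with no error at Step 1. An SB-coded loss in the band is still rejected.

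**The case against.** A reader might infer that these losses match no outcome and drop out. The protocol does not support that: outcomes come from codes, the assessment hierarchy and the Table 1 spacing, and gestation plays no part. Only the start date is affected.

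A reader might also infer that every such start is two months wrong. That is only the Step 5 default. If GEST holds completed weeks and the day within the week at recording is uniform (both assumptions), SA acceptance requires that remainder to be at least g − 134. That passes 7 + 6 + 5 + 4 + 3 + 2 = 27 of 42 combinations of gestation and remainder, or 64%. Some nuchal, AFP and Step 6 dates also shrink the error.

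The reach is narrow. The protocol expects an LMP in about 50% of CPRD live births and in no US claims live births; it gives no such figure for losses. GEST is present in 1.4% of Optum live births. The band is six days wide. The rule-out filter for SA (antenatal visit, confirmation or complication record within 42 days) may remove some late losses before dating, although its final clause names ECT instead of SA. Table 2 is also said to rest on outcome-specific research and in-house clinical validation, which cannot be seen here.

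All of this limits the size of the problem and stands. None of it explains the gap. The profile review does assess start dates by outcome, but 50 profiles per outcome in CPRD and Optum may contain few or no losses from so narrow a band, and no sensitivity analysis is planned.

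**Conclusion.** The point holds as an internal inconsistency with a bounded effect. Table 2's limits conflict with their own definitions for days 134 to 139, and under Steps 1 to 5 a correct recorded start there is rejected whether the loss is coded SA or SB. Where no other accepted date or Step 6 marker intervenes, the start is 64 to 69 days late (SA) or 57 to 62 days early (SB, preterm or no term record). The GEST formula extends the problem to a recorded 20 weeks on the outcome date.

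This rests on inclusive limits and, for the GEST results on true gestation, on completed weeks. The documents give no count of affected episodes; it is probably small, and the loss of a recorded LMP is mainly a CPRD matter. The overall outcome counts are not threatened. It is worth correcting before the single standard program is run.

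**What to change.** 1. Set the SA maximum term in Table 2 to 139 days so that the SA and SB windows meet. The existing bound at prior outcome plus retry count stays.
2. Reconcile the 140-day SB and DELIV minimum with the one-day addition in the GEST formula, so that 20 weeks recorded on the outcome date is not rejected. If this is done by lowering the minimum, check Table 1 as well: its 168 and 154 days equal 140 + 28 and 140 + 14.
3. For SA- and SB-coded episodes whose recorded LMP or GEST start falls outside the window, flag them and report the count by database. This matters for SB-coded losses at 134 to 139 days, which item 1 does not repair.
4. Do not accept out-of-window starts without an upper limit. For a woman with no recorded prior outcome, that could admit an LMP from an earlier, unrecorded pregnancy.

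The cost is one table value, one rule to align, and one flag with a count. The downside is a search back for SA that is six days longer (139 − 133).
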